## **20.0 Prior Approvals**

Prior approval for this study will be obtained from the LI Human Subject Committee and the LI CTSI/CTRC.

## **21.0 Recruitment Methods**

**21.1** Potential subjects will be recruited through the study physicians' and other MPS physicians' clinical practices, as well as advertisements on MPS foundation websites including that of the Cure Sanfilippo Foundation and the ConnectMPS patient registry. The study will be registered on clinicaltrials.gov. Information on the study will be shared through social media as well. For out-of-state participants, the study will be initially discussed by phone and, if they are interested in participation, we will combine the Screening and Week -8 visits, getting written consent/assent at the beginning of the visit. Patients and/or their parents or legal guardians will be given the option of receiving copies of the consent/assent by email, mail, or fax for further review prior to their Screening/Week -8 visit. The study coordinator will then contact the patient or parents/legal guardians within a few days to schedule a Screening/Week -8 visit if they are interested in participating.

## **22.0 Local Number of Subjects**

About 20 subjects will take part in this study.

## **23.0 Provisions to Protect the Privacy Interests of Subjects**

Study data and information will be kept confidential and managed in accordance with requirements of Health Insurance Portability and Accountability Act of 1996 (HIPAA). All data will be stored in locked offices and not released without subject permission.

Subjects will interact with and provide personal information to only individuals who are on the study site delegation log or employees of the CTRC. All individuals interacting

with study subjects and their caregivers will have successfully completed HIPAA training.

The research team will obtain Authorization for Release of Protected Health Information (PHI) from the subject or subject's parent or guardian to permit them to access medical information about the subjects.

#### **24.0 Compensation for Research-Related Injury**

Subjects will get medical treatment if they are injured as a result of taking part in this study. The cost of this medical treatment will be the responsibility of the subject/subject's parent/guardian. The cost will not be covered by the study.

#### **25.0 Economic Burden to Subjects**

Subjects will not be responsible for any costs directly related to their participation in this study. Indirect costs as a result of participation in this study, such as loss of work days, will be the responsibility of the subject or the subject's parent or guardian.

#### **26.0 Consent Process**

Each subject, subject's parent, or subject's legal guardian will be provided a consent form describing this study and providing sufficient information to make an informed decision about their participation in this study. The consent form will be submitted with the protocol for review and approval by the IRB for the study. The formal consent of an adult subject or minor subject's parent/legal guardian, using the IRB-approved consent form, must be obtained before that subject is submitted to any study procedure. This consent form must be signed by the subject or parent/legal guardian, and the Investigator-designated research professional obtaining the consent. A blank copy of the IRB-approved form must be kept on-site by the Investigator.

Assent must be obtained from all minor subjects aged 7 to 17 years who are cognitively able to give assent, in addition to the informed consent of the parent/legal guardian in accordance with Federal Regulations and the IRB.

##### **26.1 Subjects who are not yet adults**

Subjects in the United States are considered minors if they are 17 years or younger, with the exception of Alabama (19 years), Nebraska (19 years or upon marriage), and Mississippi (21 years).

Parental permission will be obtained for minors from one parent even if the other parent is alive, known, competent, reasonably available, and shares legal responsibility for the care and custody of the child.

Parental or guardian (as defined by Department of Health and Human Service [DHHS] and FDA regulations) consent will be obtained. A guardian must provide written documentation of the legal ability to consent to for the child's participation in research. A copy of this documentation will be kept with the consent document.

### ***26.2 Cognitively Impaired Adults /Adults Unable to Consent***

The individuals from whom permission will be obtained are the following in descending order of priority:

- The person's agent pursuant to an advance health care directive
- The conservator or guardian of the person having the authority to make health care decisions for the person
- The spouse of the person
- An individual as defined in Section 297 of the Family Code
- An adult son or daughter of the person
- A custodial parent of the person
- Any adult brother or sister of the person
- Any adult grandchild of the person
- An available adult relative with the closest degree of kinship to the person

### ***26.3 The process for assent of the subjects***

Assent will be attempted for all subjects age 7-17 years and for cognitively impaired adults. The process for assent will include reviewing the assent document with the subject and their parent/guardian in a verbal face-to-face discussion, asking them for questions and discussing these, then asking the subject to sign and date the assent document if they would like to participate in the study.

Assent will be documented in a progress note.

Should a child enroll at the age of 5 years, assent will be obtained once the child is 7 years old and capable of providing it. Should a child enrolled in the study reach 18 years during the study, consent will be obtained from them at that time.

### ***26.4 Process to Document Consent in Writing***

We will be following "SOP: Written Documentation of Consent (HRP-091)"

### **26.5 Vulnerable Populations**

We will include the following special populations:

- Adults unable to consent – yes, a separate consent has been prepared for the guardian of these adult subjects.
- Individuals who are not yet adults (infants, children, teenagers) – yes, a separate consent has been prepared for the parent/guardian of these pediatric subjects as well as an assent form that will be completed with all pediatric subjects age 7 and older.
- Pregnant women - no
- Prisoners – no

## **27.0 Specific Drug Supply Requirements**

### **27.1 Drug Receipt**

Kineret™ is supplied in single-use preservative free, prefilled glass syringes with 27-gauge needles. Each prefilled glass syringe contains 100 mg of anakinra per 0.67 mL. The full syringe contains 100 mg anakinra. Anakinra will be ordered by the Investigational Drug Service (IDS) at LI. Study drug inventory will be documented.

### **27.2 Packaging**

The immediate package of an investigational drug intended for human use shall bear a label with the statement:

Caution: New Drug--Limited by Federal law to investigational use.

### **27.3 Storage**

Vials of anakinra will be stored at 2-8°C, protected from light.

### **27.4 Dispensing of Study Drug**

Drug will be provided by Sobi and dispensed by the LI IDS, who are experienced in the safe and proper handling of study drug. Medication will be dispensed in accordance with the protocol. The Investigator and IDS will keep

accurate records of the medications, the amount dispensed to and returned by the patients, and the disposition at the end of the study.

### **27.5 Parent Training**

Parents will be trained on administration of the study drug during their Day 1 study visit and required to independently administer the injection on Day 2 before being discharged home. Parents will then administer the drug daily at home.

Parents will be educated on signs and symptoms of anaphylaxis and instructed on procedures for obtaining local medical care in the event of anaphylaxis (e.g. oral diphenhydramine, IM epinephrine, and call 911) or other study drug related concerns (contact study MD on call, local MD, or go to local ED or Urgent Care Clinic). Diphenhydramine and epinephrine will be dispensed to the families to take home with them, with instructions on the use of these for treatment of allergic reactions including anaphylaxis.

### **27.6 Return or Destruction of Study Drug**

At the completion of the study, there will be a final reconciliation of study agents that were shipped, consumed, and remaining. This reconciliation will be logged on the drug reconciliation form, signed and dated. Any discrepancies noted will be investigated, resolved, and documented prior to return or destruction of unused study drug. Drug destroyed on site will be documented in the study files. The Investigational Pharmacy will be responsible for the destruction of medication at conclusion of the study or upon drug expiration.

### **27.7 Dosing**

In this study anakinra subcutaneous (SC) will be administered at a dose level of 100 mg SC once daily. Anakinra will be administered every other day in patients who have severe renal insufficiency or end stage renal disease (defined as creatinine clearance < 30 mL/min as estimated from serum creatinine levels).

**Dose will be increased to 200 mg SC once daily**, with a maximum dose limit of 8 mg/kg/day, at **Week +8** if the change in at least one of the two most bothersome outcomes selected by the parents/guardians at the Day 1 visit has not improved by  $\geq$  the MCID as defined in Section 9.1. If the MCID is not achieved after 8 weeks on maximum trial dose of 200mg (max dose 8 mg/kg/day), **treatment with anakinra may be discontinued after a review and discussion between the study PI and subject's parent(s) of their child's individual results from all study outcome measures.**

**Dose will be increased to 200 mg SC once daily**, with a maximum dose limit of 8 mg/kg/day, at **Week +16** if the change in at least one of the two most bothersome outcomes selected by the parents/guardians at the Day +1 visit have worsened by  $\geq$  the MCID as defined in Section 9.1 between week +8 and week +16, after an improvement from Day +1 to week +8. If the MCID is not achieved after 8 weeks on maximum trial dose of 200mg (max dose 8 mg/kg/day), **treatment with anakinra may be discontinued after a review and discussion between the study PI and subject's parent(s) of their child's individual results from all study outcome measures.**

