**For example:**

- At week +8, if a subject has not improved in the chosen items then the dose will be increased to 200 mg SC daily.
- At week +8, if a subject has improved, then the dose stays at 100 mg SC daily. However, if this individual then has worsening of the two most bothersome outcomes from week +8 to week +16, after improving from day 1 to week +8, the dose will be increased to 200 mg SC daily at that point (i.e. increase at week +16 after not increasing at week +8).

**Dose will be decreased by 50 mg SC once daily** at any time throughout the study if a participant develops any of the following:

- Neutropenia  $<1200$  cells/microliter persistent for  $\geq 2$  weeks
- Thrombocytopenia  $<50 \times 10^9$  platelets/liter persistent for  $\geq 2$  weeks
- Mild/moderate hypersensitivity reactions including urticaria, rash, and pruritis
- Participants develops a CTCAE grade 3 AE

**Anakinra will be stopped** if the AE above does not resolve within 2 weeks of decreasing the dose by 50 mg SC once daily. Anakinra will be restarted at 0.5 times the last dose administered once the AE is resolved. If the AE recurs with restarting anakinra, it will be discontinued and the subject monitored per protocol.

The starting dose is the same dose level as recommended for adult rheumatoid arthritis patients. The dose escalation is within the range of the recommended dose in Neonatal onset multisystem inflammatory disease (NOMID), including also pediatric patients, is related to body-weight, with a recommended starting dose of 1-2 mg/kg up to a maximum dose of 8 mg/kg.

Smaller children with lower body weight need higher dose levels/kg body-weight in order to achieve similar anakinra serum exposure as in older, heavier children, due to a higher capacity to eliminate anakinra/kg body-weight, based on pharmacokinetic data in 22

systemic-onset juvenile idiopathic arthritis (SJIA) pediatric patients in the age range 2-17 years.

As an example, based on this study, a patient with a body-weight of 20 kg is predicted to require a dose of 4 mg/kg/day to achieve similar anakinra exposure (area under the curve [AUC]0-24h, ss and Cmin, ss) as a dose of 100 mg in a 50 kg patient. Additional examples are given below:

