#### Predicted exposure of anakinra in three hypothetical patients

|        | Anakinra 2 mg/kg/day (max 100 mg)      |                                  | Anakinra 4 mg/kg/day (max 200 mg)      |                                  |
|--------|----------------------------------------|----------------------------------|----------------------------------------|----------------------------------|
| BW     | AUC 0-24h,ss *
(ng·h/mL) | C min,ss *
(ng/mL) | AUC 0-24h,ss *
(ng·h/mL) | C min,ss *
(ng/mL) |
| 20 kg  | 11561                                  | 95                               | 23121                                  | 191                              |
| 50 kg  | 18776                                  | 236                              | 37552                                  | 472                              |
| 100 kg | 13556                                  | 212                              | 27111                                  | 424                              |

\* Predicted steady-state exposure based on the following published population PK parameters for anakinra (Urien et al 2013):  
 $k_a = 0.38 \text{ (h}^{-1}\text{)}$ ;  $CL/F = 0.847 \times (BW/70)^{0.47} \text{ (L/h)}$ ;  $V/F = 2.581 \times (BW/70)^{0.76} \text{ (L)}$

The patients to be included in the current study will be age 4 years and older. Given that the pharmacokinetics of anakinra in children support a higher dose level/kg body-weight the same daily dose 100 mg anakinra is planned for this study. The planned daily anakinra dose 100 mg will be within the recommended dose range for anakinra in pediatric patients.

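### Section 27.7 caps the escalated dose at 8 mg/kg/day but not the flat 100 mg start, so a participant under 12.5 kg, if one enrols, would start above the protocol's own maximum

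*Protocol*

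**What the plan says.** All of the relevant text is in the Protocol.

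- **Start (27.7).** "In this study anakinra subcutaneous (SC) will be administered at a dose level of 100 mg SC once daily". The only adjustment at the start is every-other-day dosing in severe renal insufficiency.
- **Limit (27.7 and 9.1).** The increases to 200 mg at Week +8 and Week +16 each come "with a maximum dose limit of 8 mg/kg/day". Both sections attach the same figure to the 200 mg maximum trial dose.
- **Source of the limit (27.7).** The range cited for another paediatric indication, NOMID, runs "up to a maximum dose of 8 mg/kg".
- **Who may enter (5.2, 5.3, 27.7).** "The patients to be included in the current study will be age 4 years and older". Neither the inclusion nor the exclusion criteria set a minimum weight. Only the general investigator-discretion exclusion could catch a very small child.
- **Assurance (27.7, after the exposure table).** "The planned daily anakinra dose 100 mg will be within the recommended dose range for anakinra in pediatric patients". No weight condition is attached.
- **Rationale (27.7).** "Smaller children with lower body weight need higher dose levels/kg body-weight", in order to reach exposure similar to that of heavier children.

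**The concern.** A flat dose combined with a per-kilogram ceiling has a weight below which the two collide. The protocol handles this for the 200 mg step by writing in the ceiling, but does not do so for the 100 mg step. If a participant fell below the collision weight, three things would follow:

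- Dosing from Day 1 would be above the maximum that the protocol itself states.
- The assurance about the recommended range would be false for that participant.
- The escalation instruction would fail. A participant who met the Week +8 criterion, which Section 9.1 ties to the Phase 2 primary endpoint, would have to be given more drug under a ceiling that requires less.

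**Working it through.** **Inputs.** Start 100 mg, escalated dose 200 mg and ceiling 8 mg/kg/day (27.7). Clearance proportional to (weight/70)^0.47 (footnote to the exposure table in 27.7).

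**1. Collision weights.** Weight = dose / ceiling.
- Start: 100 / 8 = 12.5 kg.
- Escalated dose: 200 / 8 = 25 kg. The stated cap already deals with this one.

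**2. Start and permitted escalated dose by weight.** Start per kg = 100 / weight. Permitted escalated dose = min(200, 8 × weight).

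| Weight (kg) | Start (mg/kg) | Permitted escalated dose (mg) | Change from 100 mg |
|---|---|---|---|
| 10 | 10.0 | 80 | −20 |
| 11 | 9.1 | 88 | −12 |
| 12 | 8.3 | 96 | −4 |
| 12.5 | 8.0 | 100 | 0 |
| 16 | 6.25 | 128 | +28 |
| 20 | 5.0 | 160 | +60 |
| 25 | 4.0 | 200 | +100 |

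Below 12.5 kg the start is over the ceiling and the increase is negative. At 12.5 kg exactly, the increase is zero.

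**3. Check of the protocol's exposure table.** At 20 kg and 40 mg, dose / clearance with the printed constant of 0.847 L/h gives 85,092 ng·h/mL. The table prints 11,561, a factor of about 7.36, and the other AUC cells differ by about the same factor. The absolute values therefore do not reproduce, but ratios do. Scaling the table's 20 kg row to 100 mg gives 11,561 × 100/40 = 28,903, and 28,903 / 18,776 = 1.54. The exponent gives (50/20)^0.47 = 1.54. Only ratios are used below.

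**4. Relative exposure at the edge.** AUC is proportional to dose / weight^0.47.
- 100 mg at 12 kg against 100 mg at 50 kg: (50/12)^0.47 = 1.96.
- 100 mg at 12 kg against 200 mg at 50 kg: 1.96 / 2 = 0.98.
- 100 mg at 10 kg against 200 mg at 50 kg: (50/10)^0.47 / 2 = 2.13 / 2 = 1.07.
- 200 mg at 25 kg, which is exactly 8 mg/kg and permitted, against 200 mg at 50 kg: (50/25)^0.47 = 1.39.

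On predicted AUC, even the 10 kg case (1.07) lies below a case that the protocol allows (1.39). These figures extend the footnote's exponent below 20 kg, the lightest weight tabulated.

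**The case against.** **No such participant may exist.** This stands. The protocol gives no weights, so everything depends on someone aged 4 or older weighing under 12.5 kg.

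**The ceiling can be read as trial-wide.** Sections 27.7 and 9.1 attach it to the maximum trial dose, so a pharmacist might apply it to any dose. That reading does not close the gap. It turns an uncapped start into a flat 100 mg instruction that contradicts the ceiling below 12.5 kg.

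**The pharmacokinetic rationale supports more mg/kg in small children.** This stands in part. A reader might infer that the rationale stops at 20 kg because that is the lightest row of the table. The rows are labelled hypothetical, and the cited data are from 22 patients aged 2–17 years whose weights are not given, so the inference is unsupported. The rationale still does not lift the 8 mg/kg maximum that the protocol adopts.

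**Other safeguards exist.** There is monitoring after the dose on Days 1 and 2, safety laboratory tests at Weeks +2 and +4, reductions of 50 mg for listed events, and the discretionary exclusion. These soften the consequence, but none is a weight rule.

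**The worked examples in 27.7.** They say "At week +8, if a subject has not improved in the chosen items then the dose will be increased to 200 mg SC daily" and "the dose will be increased to 200 mg SC daily at that point" without repeating the ceiling. A reader might infer that they permit 200 mg below 25 kg, for example 200 mg rather than 160 mg at 20 kg. They directly follow rules that state the ceiling and only illustrate when to escalate, so they do not override it.

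**Conclusion.** The point holds as a minor, conditional defect. For any eligible participant under 12.5 kg, Section 27.7 as written gives a start above the protocol's stated maximum, makes its range assurance untrue, and leaves an escalation rule that cannot be followed. The 12.5 kg threshold is exact arithmetic and rests on no assumption. The number of participants affected is unknown and may be zero of 20.

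A reader might infer that such a child would be over-exposed. The documents do not show this: predicted AUC at 12 kg is about 0.98 of that from the permitted 200 mg at 50 kg. Nor is any effect on the analysis or on the interpretation of results shown.

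**What to change.** State in Section 27.7 that 8 mg/kg/day applies to every dose:

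- start = min(100 mg, 8 mg/kg);
- escalated dose = min(200 mg, 8 mg/kg).

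Make the closing sentence about the recommended range conditional on that limit. With the cap, the start becomes 80 mg at 10 kg, 88 mg at 11 kg and 96 mg at 12 kg, and stays at 100 mg from 12.5 kg upward. Repeating the ceiling in the worked examples is optional wording.

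The cost is one sentence and a short qualification. Weight is already measured at the Day +1 visit (Section 10.2). Doses other than whole 100 mg syringes are already needed for the capped escalation and the 50 mg reductions. The only downside is weight-based preparation of the start dose for a participant under 12.5 kg, if one enrols.

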## 9.0 Study Endpoints

### 9.1 Primary and secondary endpoints.

#### Primary endpoints:

Phase 1: Incidence of treatment-emergent adverse events and laboratory values over 8 weeks of treatment to known frequency of anakinra-related AEs in other populations.

Phase 2: Need for dose escalation as determined by within individual change over 8-week treatment period compared to change over 8-week observational period in the 2 most bothersome symptoms for each enrolled patient, selected from measures for the MDRI. Choices are below in bold. These 2 symptoms will be monitored by one or more of the assessments below. If the Minimal Clinically Important Difference (MCID) that is defined below is not achieved after 8 weeks of treatment, or there has been a decrease of more than the MCID between 8 and 16 weeks after an increase greater than MCID at week 8, the dose will be escalated (see Section 27.7). If the MCID is not achieved after 8 weeks on maximum trial dose of 200mg (max dose 8 mg/kg/day), treatment with anakinra may be discontinued (see Section 27.7).

- Sanfilippo **Behavior** Rating Scale (SBRS): MCID = 0.25 SD for each scale
  - Symptoms described in table below:

|                         |                                                                                                                                        |                           |
|-------------------------|----------------------------------------------------------------------------------------------------------------------------------------|---------------------------|
| Body Movements          | Makes large complex movements of their body, such as spinning, twirling or repeatedly bouncing up and down.                            | Movement                  |
| Object Interaction      | Examines or manipulates some novel or unfamiliar objects repeatedly.                                                                   |                           |
| Activity/Routines       | Never plays with one object or engages in one activity for very long.                                                                  |                           |
| Emotional Function      | Expresses emotions inappropriate to the situation.                                                                                     | Social/emotional function |

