- Autism **Parenting Stress** Index (APSI): MCID = 0.25 SD for Stress Total 
  - Ability to communicate
  - Tantrums/meltdowns
  - Self-injurious behavior
  - Difficulty making transitions from one activity to another
  - Toilet training
  - Not feeling close to your child
  - Concern for your child not being accepted by others
  - Concern for the future for your child living independently
- PROMIS **Fatigue** - Parent Proxy Custom Short Form: MCID = 3-point change
- **Seizures** – Parents will record each seizure in a seizure journal provided by the study. Information recorded will include the duration (average length of seizure), and need for medical intervention (e.g. rescue medication, medical evaluation).

- **Movement** disorder (e.g. dystonia, chorea, etc.) – Parent reported duration and severity. Change in one of two characteristics for +/-1 score, +/-2 score for change in two of the characteristics.
- Non-communicating Children's **Pain** Checklist-Revised (NCCPC-R): MCID = 0.25 SD

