## 12.2 Analysis

### **Primary objective**

Outcome variables include AEs/tolerability, 2 most bothersome symptoms, and multi-domain responders index (MDRI) as described in section 9.1. Binary AEs such as hospitalization ( $\geq 1$ ) will be summarized using frequencies/rates by the two period (pre-observation, treatment). The multiple event such as the total number of seizures will be summarized using median with the inter-quartile range (IRQ). For testing changes between the two periods, the McNemar's test (binary event) or Wilcoxon Signed Rank test (multiple events and MDRI) will be used. For continuous outcomes such as laboratory results, a paired t-test and a repeated measures ANOVA will be used. Residual analyses will be conducted to check the model assumption. If it violates assumption, Friedman test (nonparametric) will be used instead.

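### Need for dose escalation, the Phase 2 primary endpoint, is defined inconsistently in Protocol Sections 9.1 and 27.7 and does not appear in the Section 12.2 analysis

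*Protocol*

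**What the plan says.** Protocol Section 9.1 sets the Phase 2 primary endpoint as "Need for dose escalation as determined by within individual change over 8-week treatment period compared to change over 8-week observational period" in the two most bothersome symptoms. It then gives an operating rule with two limbs and refers to Section 27.7. The first limb is that the MCID "is not achieved after 8 weeks of treatment". The second is that "there has been a decrease of more than the MCID between 8 and 16 weeks after an increase greater than MCID at week 8". Neither limb says whether one symptom or both must qualify.

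Section 27.7 states the rule again. At Week +8 and at Week +16 it escalates "if the change in at least one of the two most bothersome outcomes" meets the criterion: not improved by at least the MCID at Week +8, or worsened by at least the MCID between Week +8 and Week +16 after an improvement. The worked examples that follow read differently. For Week +8: "if a subject has not improved in the chosen items then the dose will be increased". For Week +16, the dose rises "if this individual then has worsening of the two most bothersome outcomes from week +8 to week +16".

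On seizures, Section 9.1 prints the symptom in bold as one of the choices and says "Parents will record each seizure in a seizure journal provided by the study", but gives no MCID or score. Section 3.0 lists seizures in the MDRI. The MDRI list under the secondary endpoints in Section 9.1 omits them, yet the scoring paragraph there says they are scored as already described.

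Section 12.2, under the primary objective, says: "Outcome variables include AEs/tolerability, 2 most bothersome symptoms, and multi-domain responders index (MDRI) as described in section 9.1". It does not mention escalation. It also states that the primary outcome, in the singular, is tested at the 5% level.

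**The concern.** The same rule decides which children are escalated and what is reported as the Phase 2 result. If two readers can apply it differently to identical data, the endpoint is not reproducible. A child who worsens in one symptom only between Week +8 and Week +16 is escalated under the rule, but does not fit the example. A family that picks seizures has no threshold at all. Because Section 12.2 names no estimate for the endpoint, nothing in the Protocol fixes which version will be reported. With an MCID of 0.25 SD, many children will miss the criterion through measurement noise alone, so a high escalation count is hard to interpret without a stated rule and interval.

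**Working it through.** **The plan's own figures.** Section 12.3 gives no figure for escalation. Its margin of 13% to 18% is for adverse-event proportions of 5% to 15% with n = 20. A continuity-corrected Wilson interval has half-widths of 13.3% and 17.5%. The half-SD margin for paired differences also reproduces: t(0.975, 19)/√20 = 0.47 SD. Neither figure is in dispute.

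**The texts side by side.**

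| Point | 9.1 | 27.7 rule | 27.7 example |
|---|---|---|---|
| Week +8, one or both | not stated | at least one | chosen items, plural; no MCID |
| Week +16, one or both | not stated | at least one | the two |
| Comparator | observation period in the endpoint sentence | none | none |
| Week +16 loss | more than the MCID | at least the MCID | worsening, size not stated |
| Prior gain | greater than the MCID | an improvement, size not stated | improving, size not stated |

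**Size at Week +8.** The Protocol gives no per-symptom variability, so the following are assumptions: test-retest correlation r, MCID 0.25 SD, normal scores.

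- SD of change = √(2(1 − r)). At r = 0.8 this is √0.4 = 0.632.
- With no drug effect, P(one symptom improves by at least the MCID) = 1 − Φ(0.25/0.632) = 0.346.
- If one failure is enough, with independent changes: 1 − 0.346² = 0.88. If both must fail: (1 − 0.346)² = 0.43. The gap is 2 × 0.346 × 0.654 = 0.45, or about 9 of 20 subjects.
- For r = 0.7 to 0.9 the two readings give 86% to 92% and 39% to 51%.
- With a true benefit of 0.5 SD, p = 0.654, and the figures are 57% and 12%.

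Both symptoms are caregiver-reported, so their changes may well be correlated. At r = 0.8 with no effect (bivariate normal):

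| Correlation of the two changes | One fails | Both fail | Gap (points) |
|---|---|---|---|
| 0 | 88% | 43% | 45 |
| 0.3 | 84% | 47% | 37 |
| 0.5 | 81% | 50% | 31 |
| 0.7 | 77% | 54% | 23 |

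**Size at Week +16.** Assume a per-symptom worsening probability q of 0.1 to 0.3 among eligible subjects, independent. At least one worsens: 1 − (1 − q)² = 19% to 51%. Both worsen: q² = 1% to 9%.

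**Effect of the comparator.** If treatment change is judged net of observation-period change, the SD of the difference is √(6(1 − r)) = √1.2 = 1.095 at r = 0.8. Then p = 1 − Φ(0.25/1.095) = 0.41, and the two readings give 83% and 35%. These figures ignore the selection of symptoms at Day 1.

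**Can the observation period serve as a tested control?** Section 27.7 has the symptoms chosen at Day 1, which is both the end of the observation period and the treatment baseline. Simulate six independent domains, r = 0.8 and no drug effect, with the two worst at Day 1 chosen. The criterion is met by about 94% before and 78% during treatment if one failure is enough, and by 58% and 29% if both must fail. The apparent benefit is regression to the mean.

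**The case against.** The strongest reply is that Section 27.7 is clear: it says at least one at both time points, Section 9.1 defers to it, and the examples are only examples. A child who has failed in both symptoms also satisfies a rule that needs only one. That stands in part. A reader might infer that the Week +8 rule and example flatly contradict each other; they do not, and ambiguity is the right word. At Week +16 the example can also be read as a special case. But it presents the condition for escalating a child who had improved, and it names both outcomes where the rule names one.

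It is also fair that the operating sentence in Section 9.1 carries no comparator. This leaves Section 9.1 inconsistent with its own endpoint sentence, so it does not settle the matter.

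A reader might infer that Section 12.2 has wrongly promoted the MDRI. It follows primary objective 2 in Section 3.0; the mismatch is with the secondary listing in Section 9.1. The two symptoms on which escalation depends are also named in Section 12.2. A separate analysis plan may hold more detail, but Section 12.2 itself lists the variables for the primary objective, and the endpoint is not among them.

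Finally, this is an open-label pilot of 20, sized by feasibility. That limits what can be concluded from it, but does not excuse an endpoint that can be scored two ways.

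**Conclusion.** The point holds as an inconsistency in the definition and a missing link to the analysis. The conflict is clearest at Week +16 and in the comparator and thresholds. The seizure gap and the absence of the endpoint from Section 12.2 are plain on the text.

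On the stated assumptions, the choice between one and both symptoms moves the Week +8 figure by about 23 to 45 points, or roughly 5 to 9 of 20 subjects. The 45-point figure should not be read as established: it needs independent changes. The 0.25 SD MCID applies only to the SBRS, APSI and NCCPC-R; the CSHQ, PROMIS fatigue and movement items use other thresholds. Section 9.1 also does not state a proportion as its result. The proportion is used here as the natural summary of a yes/no endpoint.

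The documents do not support a claim that any one of the rules is the correct one, and none is made here.

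**What to change.** 1. Reconcile Section 9.1, the Section 27.7 rule and its examples into one identical statement covering one or both symptoms, the comparator, the thresholds, and both Week +8 and Week +16. The sponsor chooses the content.
2. Remove seizures from the Section 3.0 list, the Section 9.1 choices and the MDRI scoring sentence, or give them a threshold and score.
3. In Section 12.2, name need for escalation under that rule as the Phase 2 primary outcome. Report the number and proportion with an exact 95% confidence interval at Week +8 and by Week +16. Section 8.0 times the primary analyses from the last Week +8 visit, so it must be aligned if Week +16 counts.
4. Give the MDRI one status across Sections 3.0, 9.1 and 12.2.
5. For subjects already dosed, tabulate the result under both readings.
6. If the chosen rule has no observation-period comparator, its rate from Week -8 to Day 1 may be shown as a descriptive reference. It should not be tested with McNemar, because of the selection at Day 1. If the rule is relative to the observation period, there is no earlier period to which it could be applied.

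The cost is wording in a few sections and one analysis paragraph. The questionnaires are already scheduled at Week -8, Day 1, Week +8 and Week +16, so no new data are needed unless seizures are kept.
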